### Dynamic balance testing

Dynamic balance will be evaluated using the Biodex Balance System. This device has established good-to-excellent intratester reliability for stability indices in healthy university students (ICC = 0.85 for SI, 0.78 for APSI, and 0.84 for MLSI during static stance) and has been widely validated for dynamic balance assessment (30). Participants will stand barefoot on the platform at stability level 8, with fixed heel coordinates and toes abducted at approximately 30 degrees. During the eyes-open test, participants will focus on the screen and attempt to keep the cursor centered for 20 s. During the eyes-closed test, the same posture and task duration will be used without visual input. Each condition will be repeated three times, and the mean value will be used for analysis. SI, APSI, and MLSI will be extracted. Lower index values indicate better balance capacity (31).

### Sample size

The sample size will be estimated using PASS 15.0 software. Knee extensor peak torque will be selected as the primary outcome for sample size calculation. Based on relevant preliminary and published experimental data, the expected mean and standard deviation of post-intervention knee extensor peak torque in the three groups will be used to estimate an effect size of Cohen’s *f* = 0.55. With a two-sided alpha level of 0.05, statistical power of 0.90, and one-way analysis of variance for three-group comparison, the minimum required sample size is 16 participants per group. Allowing for an anticipated dropout rate of approximately 15%, 19 participants will be enrolled in each group, yielding a total sample size of 57 participants (32).

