### Randomization and allocation concealment

After baseline assessment, eligible participants will be randomly assigned to three groups (Tai Chi Chuan group (TCC), unstable resistance training group (URT), or Tai Chi Chuan combined with unstable resistance training group (T + URT)) in a 1:1:1 ratio using simple randomization. The randomization sequence will be generated by an independent statistician using SPSS (version 25.0, IBM Corp., Armonk, NY, USA). Allocation details will be sealed in sequentially numbered, opaque envelopes. A research assistant not involved in outcome assessment will open the envelopes after baseline testing, just before the first intervention session.

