### Statistical analysis

Two analysis sets will be used. The intention-to-treat set will include all randomized participants in their originally allocated groups regardless of adherence or withdrawal. The per-protocol set will include participants who complete the full intervention protocol without major protocol deviations. The primary analysis will be based on the intention-to-treat principle, and the per-protocol analysis will be used as a sensitivity analysis.

Missing data will be handled using multiple imputation when the missingness mechanism is considered missing at random. Baseline knee muscle strength, dynamic balance index values, age, height, and weight will be considered predictor variables for imputation. Five imputed datasets will be generated using a multiple linear regression model in SPSS 25.0. Pooled estimates will be calculated according to Rubin’s rules. If missing data are minimal, complete-case analysis may be reported as a supplementary analysis.

Categorical variables will be expressed as n (%). Normally distributed quantitative variables will be presented as mean ± standard deviation, and non-normal data as median (interquartile range). Normality will be tested with the Shapiro–Wilk test, and variance homogeneity with Levene’s test. For within-group pre–post comparisons, paired t-tests will be used for normally distributed data; otherwise, Wilcoxon signed-rank tests will be applied. Between-group differences will be assessed using one-way ANOVA for parametric data, followed by Bonferroni-adjusted pairwise comparisons when the overall effect is significant. Non-parametric data will be analyzed with the Kruskal–Wallis test, followed by Dunn–Bonferroni pairwise comparisons. Categorical variables will be compared using the chi-square test or Fisher’s exact test. Given three primary outcomes (knee extensor peak torque, knee flexor peak torque, and hamstring-to-quadriceps ratio), a Bonferroni correction will be applied to control multiplicity, with a significance threshold set at *p* < 0.017 (0.05/3). Secondary outcomes are exploratory, a two-sided *p* < 0.05 will be used without multiplicity correction.

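### The sample size is calculated at alpha 0.05, but each primary outcome is tested at p < 0.017, so 16 evaluable per group gives about 82% power, not 90%

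*Protocol article*

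**What the plan says.** **Sample size section.** One outcome drives the calculation: "Knee extensor peak torque will be selected as the primary outcome for sample size calculation". Expected post-intervention means and standard deviations in the three groups "will be used to estimate an effect size of Cohen’s *f* = 0.55". The test conditions are "With a two-sided alpha level of 0.05, statistical power of 0.90, and one-way analysis of variance for three-group comparison", and the result is that "the minimum required sample size is 16 participants per group". Dropout is then added: "Allowing for an anticipated dropout rate of approximately 15%, 19 participants will be enrolled in each group, yielding a total sample size of 57 participants".

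**Statistical analysis section.** Knee extensor peak torque, knee flexor peak torque and the hamstring-to-quadriceps ratio are all primary. Because there are three of them, "a Bonferroni correction will be applied to control multiplicity, with a significance threshold set at" p < 0.017, given as 0.05/3. The between-group test is a one-way ANOVA, with Bonferroni-adjusted pairwise comparisons if the overall test is significant.

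The abstract and Table 5 list the same three primary outcomes. Nothing elsewhere in the article links the two alpha levels.

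**The concern.** The two sections describe the same test on the same outcome at different significance levels. A stricter threshold lowers power at a fixed sample size, so the 90% and the minimum of 16 per group do not describe the analysis that will decide the trial.

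This affects how a negative result is read. The Discussion says that finding no added benefit would be as informative as finding one. How informative it is depends on the type II error, and the article understates that error for the outcome on which the trial was sized.

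This is not a detail left to a separate analysis plan. Both alpha levels are fixed in this article, and they conflict.

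**Working it through.** **Inputs**

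- Groups: k = 3, allocated 1:1:1 (Randomization and allocation concealment).
- Effect size f = 0.55, target power 0.90, planning alpha 0.05, n = 16 per group, dropout 15%, 19 enrolled per group (Sample size).
- Testing alpha: 0.05/3 = 0.0167, printed as 0.017 (Statistical analysis).

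**Formula.** For a one-way ANOVA with n per group, the F statistic has 2 and 3n − 3 degrees of freedom and, under the alternative, noncentrality λ = 3n·f². Power is the probability that this noncentral F exceeds the central F critical value at the chosen alpha.

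**Step 1: reproduce the plan at alpha 0.05**

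- n = 15: λ = 45 × 0.3025 = 13.61, power 90.0%.
- n = 16: λ = 48 × 0.3025 = 14.52, df = (2, 45), critical F = 3.20, power 92.0%.

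The smallest n is 15 against the stated 16. Rounding of f explains the difference: f = 0.545, which rounds to 0.55, needs exactly 16. For dropout, 16/0.85 = 18.8, which rounds up to 19, and 3 × 19 = 57. The plan's figures reproduce at its own alpha.

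**Step 2: the same design at the alpha to be used**

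At n = 16 the critical F rises from 3.20 to 4.49 while λ stays at 14.52.

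| Evaluable per group | Power at 0.05 | Power at 0.05/3 |
|---|---|---|
| 15 | 90.0% | 79.1% |
| 16 | 92.0% | 82.5% |
| 17 | 93.6% | 85.4% |
| 18 | 94.9% | 87.9% |
| 19 | 96.0% | 90.0% |

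Using the printed 0.017 instead of 0.05/3 gives 82.7% at n = 16. A simulation of 200,000 trials at n = 16 gave 92.0% and 82.5%, in agreement with the formula.

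**Step 3: what 90% would require at 0.05/3**

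- Evaluable: 19 per group.
- Enrolled with 15% dropout: 19/0.85 = 22.4, so 23 per group, 3 × 23 = 69 in total, against 57 planned.
- With 16 evaluable per group, the f detectable at 90% power is 0.604, not 0.55.

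**Step 4: sensitivity to rounding of f.** For f between 0.545 and 0.555, power at n = 16 and alpha 0.05/3 is 81.6% to 83.3%. At f = 0.545, even 19 evaluable per group gives 89.4%.

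**The case against.** The strongest reply has four parts.

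1. **Nothing in the Sample size section is miscalculated.** It states its alpha openly and its numbers follow from it. This stands: the fault is an inconsistency between two sections, not a slip in arithmetic.

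2. **Fifty-seven are enrolled, and the primary analysis is intention-to-treat with multiple imputation.** With all 19 per group observed, power at 0.05/3 is 90.0%, so 82.5% is the figure after the full planned dropout. This also stands, and the fair summary is a range of 82% to 90% depending on missing outcomes. It does not rescue the stated 90%. The article itself expects about 15% dropout, and Table 1 withdraws anyone who misses two consecutive or three cumulative sessions out of 24. Imputing post-intervention torque from baseline strength, balance, age, height and weight cannot restore the information in an unobserved outcome.

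3. **The loss is modest and inference stays valid.** The shortfall is 7.5 points from the 90% target, power remains above 80%, and the 0.017 threshold is set in advance, so type I error is unaffected. All of that is true. The article nevertheless claims 90%, and that claim does not hold for the test planned.

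4. **A baseline-adjusted analysis would recover the power.** It could. At 16 per group and alpha 0.05/3, ANCOVA power would be about 86%, 89%, 93% or 99% for a baseline–post correlation of 0.3, 0.4, 0.5 or 0.7. The article gives no such correlation and plans an unadjusted ANOVA, so these figures are illustrative and cannot be credited to the current plan.

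**Conclusion.** The concern holds. The sample size rests on alpha 0.05, whereas the outcome used to size the trial is tested at 0.05/3. At the stated 16 evaluable per group, power is 82.5% rather than 90%, and the type II error is about 17.5% rather than 10%. Measured against the 92.0% that 16 per group gives at 0.05, the loss is 9.5 points. Only with complete outcome data on all 19 per group does power reach 90%, so the uncorrected alpha uses up the whole dropout allowance.

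These figures take f = 0.55 as given and assume equal group sizes and the usual ANOVA conditions. They cover the omnibus F-test on knee extensor peak torque only. Neither 90% nor 82% is the power for the other two primary outcomes, or for the pairwise comparisons of the combined arm with each single arm that carry the main hypothesis.

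The design remains usable, but the power statement needs correcting.

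**What to change.** Rewrite the Sample size paragraph at the alpha used in the analysis, and choose one of two courses.

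- **Keep 57 participants and restate the power.** Suggested text: *For the omnibus one-way ANOVA of knee extensor peak torque, with f = 0.55 and alpha 0.017 (0.05/3), power is about 82% with 16 evaluable participants per group and about 90% if all 19 per group are analysed.* This needs no extra participants. The cost is one paragraph and a less favourable figure.
- **Keep 90% power after 15% dropout.** Enrol 23 per group, 69 in total, which is 12 more than planned.

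If the sponsor moves to a baseline-adjusted analysis, the power should be computed for that analysis from a stated and justified correlation, with a range.

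Recruitment was due to begin in May 2026. Either change should go through the process in the Protocol amendments section and be dated before any outcome data are analysed.

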### Adherence and intervention fidelity

Attendance will be recorded for every session. A participant will be considered adherent if she meets both of the following criteria:

(1) Training frequency adherence: Attendance rate ≥80%; (2) No major protocol deviation: defined as any unapproved change to the intervention content, duration, intensity, or progression that could systematically affect outcome measures, including but not limited to: (a) performing a different Tai Chi form than the 24-form simplified routine, (b) using unstable surfaces or resistance loads outside the prescribed progression in the URT protocol, (c) combining outside structured exercise programmes that interfere with the intervention effect, or (d) persistent incorrect movement patterns that, despite instructor correction, compromise training safety or fidelity. Minor deviations (e.g., occasional missed warm-up exercises, temporary heart rate outside the target zone for <10% of session time) will be recorded but will not automatically classify the participant as non-adherent.

Instructors will follow standardized checklists to ensure intervention fidelity. Heart rate and observations will verify exercise intensity and quality. Missed sessions will be followed up to support continued participation where safe.

### Participant timeline

All participants are expected to complete the trial within 8 weeks following enrollment. Recruitment and baseline assessments will begin in May 2026, with interventions and post-intervention assessments conducted consecutively. The overall schedule of enrollment, interventions, and participant assessments is illustrated in a temporal schematic diagram (Figure 3).

**Figure 3 fig3:**
[figure not shown]
Schedule of enrolment, interventions, and assessments.

### Data collection and management

Clinical and training data will be recorded on paper case report forms and then entered into an electronic spreadsheet by trained research staff. Double data entry or independent verification will be used for key variables. All electronic files will be password protected. Paper forms will be stored in locked cabinets accessible only to authorized study personnel. Participant names will be replaced by study identification codes in the analysis dataset. Data will be retained according to institutional requirements.

### Statistical analysis

Two analysis sets will be used. The intention-to-treat set will include all randomized participants in their originally allocated groups regardless of adherence or withdrawal. The per-protocol set will include participants who complete the full intervention protocol without major protocol deviations. The primary analysis will be based on the intention-to-treat principle, and the per-protocol analysis will be used as a sensitivity analysis.

Missing data will be handled using multiple imputation when the missingness mechanism is considered missing at random. Baseline knee muscle strength, dynamic balance index values, age, height, and weight will be considered predictor variables for imputation. Five imputed datasets will be generated using a multiple linear regression model in SPSS 25.0. Pooled estimates will be calculated according to Rubin’s rules. If missing data are minimal, complete-case analysis may be reported as a supplementary analysis.

Categorical variables will be expressed as n (%). Normally distributed quantitative variables will be presented as mean ± standard deviation, and non-normal data as median (interquartile range). Normality will be tested with the Shapiro–Wilk test, and variance homogeneity with Levene’s test. For within-group pre–post comparisons, paired t-tests will be used for normally distributed data; otherwise, Wilcoxon signed-rank tests will be applied. Between-group differences will be assessed using one-way ANOVA for parametric data, followed by Bonferroni-adjusted pairwise comparisons when the overall effect is significant. Non-parametric data will be analyzed with the Kruskal–Wallis test, followed by Dunn–Bonferroni pairwise comparisons. Categorical variables will be compared using the chi-square test or Fisher’s exact test. Given three primary outcomes (knee extensor peak torque, knee flexor peak torque, and hamstring-to-quadriceps ratio), a Bonferroni correction will be applied to control multiplicity, with a significance threshold set at *p* < 0.017 (0.05/3). Secondary outcomes are exploratory, a two-sided *p* < 0.05 will be used without multiplicity correction.

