### Participants

Healthy female college students will be recruited through the optional martial arts course and university announcements. Interested students will undergo eligibility screening and will provide written informed consent before enrolment (Table 1). Participants will be asked to maintain their usual diet and lifestyle during the study and to avoid initiating additional structured exercise programmes outside the assigned intervention.

**Table 1 tab1:** Eligibility criteria for study participants.

Eligibility domain	Criteria
Inclusion criteria	Female college students aged 18–22 years; normal physical examination; no history of heart, brain, or kidney disease; no recent sports injury; no regular exercise in the previous 3 months; ability and willingness to complete all tests and training; written informed consent; agreement to maintain usual diet and lifestyle.
Exclusion criteria	Abnormal body morphology or obvious limb defects that may affect testing; fracture, muscle injury, or comparable injury within the past 6 months; inability to complete the intervention because of leave, internship, transfer, or similar objective reasons; inadequate training attendance; poor compliance; any adverse condition judged by investigators to increase exercise risk.
Withdrawal criteria	(R1 Q4)Voluntary withdrawal; repeated non-attendance (defined as missing two consecutive training sessions or three cumulative training sessions); development of a condition that makes further participation unsafe (defined as the occurrence of acute exercise-related injury, severe joint pain, cardiovascular discomfort, dizziness, vomiting, or any other health problem judged by the investigator to preclude safe continued training); investigator decision based on participant safety.

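### If students withdrawn for missed sessions are not post-tested, the primary ITT analysis imputes them from baseline variables alone at near-fully-trained values, and no named analysis would show the error

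*Protocol article*

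**What the plan says.** All references are to the protocol article.

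- **Analysis set** (Statistical analysis): the primary analysis covers "all randomized participants in their originally allocated groups regardless of adherence or withdrawal".
- **Condition for imputation** (same section): multiple imputation is used "when the missingness mechanism is considered missing at random". No rule for that judgement and no other method is given.
- **Imputation model** (same section): "Baseline knee muscle strength, dynamic balance index values, age, height, and weight will be considered predictor variables for imputation". Then: "Five imputed datasets will be generated using a multiple linear regression model in SPSS 25.0". Neither treatment group nor attendance is named.
- **Checks** (same section): "the per-protocol analysis will be used as a sensitivity analysis". A supplementary complete-case analysis is possible if few data are missing.
- **Withdrawal** (Participants, Table 1): one ground is "repeated non-attendance (defined as missing two consecutive training sessions or three cumulative training sessions"). The others are voluntary withdrawal, unsafe conditions and an investigator decision on safety.
- **Attendance data** (Adherence and intervention fidelity): "Attendance will be recorded for every session". The same section counts a student as adherent at 80% attendance or more, provided there is no major deviation.
- **Dropout** (Sample size): about 15% is allowed for, which takes 16 per group to 19.

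**The concern.** An ITT analysis that keeps withdrawn students needs their outcomes, observed or imputed. The withdrawal rule selects on training received. The imputation model knows nothing about training received and takes its relation between baseline and outcome from the students who were tested. If those are only the students who stayed, a withdrawn student gets a value typical of someone who trained almost completely. The trial's premise is that training raises strength, so, given the listed predictors, such data would not be missing at random.

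At stake is the primary comparison of the combined programme with each single programme. The planned checks would not help. The per-protocol set requires completion of the intervention and a complete-case analysis requires an observed outcome, so both leave out the students whose imputed values are in doubt.

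**Working it through.** **1. The plan's own figures.** For one-way ANOVA with three groups, f = 0.55 and alpha 0.05 (noncentral F, noncentrality N × f²), 15 per group gives power 0.900 and 16 gives 0.920. Then 16 / 0.85 = 18.8, so 19 per group and 57 in total. The stated sizes reproduce. The dropout allowance means about 57 × 0.15 = 8.55, or 9 students, without an outcome: roughly 3 of 19 per arm.

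**2. Who remains under the rule.** Sessions: 8 weeks × 3 = 24 (Interventions). A third miss leads to withdrawal, so a retained student has missed at most 2 and attended at least 22/24 = 91.7%. Three misses are 21/24 = 87.5% and four are 20/24 = 83.3%. Both exceed the 80% adherence limit, yet both trigger withdrawal.

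**3. How much the rule could withdraw.** Assume independent absences with probability p per session. A student stays with no miss, one miss, or two non-adjacent misses, and there are 276 − 23 = 253 non-adjacent pairs:

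P(withdrawn) = 1 − [(1−p)^24 + 24p(1−p)^23 + 253p²(1−p)^22]

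For p = 0.05: 1 − (0.292 + 0.369 + 0.205) = 0.135 (from unrounded terms). For p = 3%, 6% and 10% the result is 4.5%, 19.3% and 45.8%. About 5.3% absence would by itself produce the planned 15% dropout. This shows that the rule could matter, not that it is the main cause of missing data.

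**4. Effect on the difference between arms.** Assumptions, in SD units:
- Means are equally spaced at f = 0.55, so adjacent arms differ by a = 0.55 × √(3/2) = 0.674.
- Fully trained gains are G + a (combined), G (comparator) and G − a (third arm), with G = 0.75 or 1.0.
- A share d of each arm is withdrawn and untested, with 3/19 in the third arm. Withdrawn students keep a share q of the gain.

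The true ITT mean of an arm with gain g is g[1 − d(1−q)]. Own-arm imputation gives g. Imputation without group gives (1−d)g + d·m, where m is the mean of tested students over all arms.

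Where two values appear, they are for G = 0.75 / 1.0.

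| Withdrawn, combined v comparator | q | True ITT difference | Own-arm imputation | Imputation without group |
|---|---|---|---|---|
| 3/19 v 3/19 | 0 | 0.567 | 0.674 | 0.567 |
| 3/19 v 3/19 | 0.5 | 0.620 | 0.674 | 0.567 |
| 5/19 v 1/19 | 0 | 0.338 / 0.286 | 0.674 | 0.490 |
| 5/19 v 1/19 | 0.5 | 0.506 / 0.480 | 0.674 | 0.490 |
| 1/19 v 5/19 | 0 | 0.796 / 0.849 | 0.674 | 0.632 |
| 1/19 v 5/19 | 0.5 | 0.735 / 0.761 | 0.674 | 0.632 |

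Worked line (5/19 v 1/19, q = 0, G = 0.75): true = 1.424 × 14/19 − 0.75 × 18/19 = 1.049 − 0.711 = 0.338.

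Without group, as listed, the error runs from 0.632 − 0.849 = −0.22 to 0.490 − 0.286 = +0.20, and is zero in the first row. With own-arm imputation it runs from 0.674 − 0.849 = −0.17 (unrounded −0.175) to 0.674 − 0.286 = +0.39.

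**The case against.** **The text does not say that withdrawn students go untested.** This stands, and it makes the finding conditional. The ITT definition keeps them in the set, and the schedule figure is not shown. Three things point towards no test: the dropout allowance, the timing of the assessment after the 8-week intervention is completed, and follow-up of missed sessions that is described only as support for continued participation. That is an inference, not a statement.

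**Attendance is one of several withdrawal routes.** This also stands. The 15% is not split by cause, so the documents do not support calling attendance the main driver.

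**Much of this is detail for an analysis plan.** This stands in part. How the mechanism is judged, what follows if the judgement fails, and the absence of a delta-adjusted analysis could all be settled in a document not shown. The predictors are described as ones to be considered, so the list may not be closed. Still, the article does commit itself to a baseline list, a number of imputations and a software package, and that list sits badly with its own withdrawal rule.

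**Tempting stronger readings.** A reader might infer that unequal withdrawal would create a spurious difference between arms. With equal gains among completers the reverse holds. Suppose a gain g in both arms, 5% versus 25% withdrawn, and half the gain kept. The true means are 0.975g and 0.875g, but own-arm imputation returns g for both, so a real difference of 0.10g is hidden. A reader might also infer that the ITT estimate must drift towards the completers' effect. That needs treatment group in the imputation model. Without it the arms are pulled together.

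**Adding attendance as a predictor would not repair this alone.** Correct: with outcomes only at 22 to 24 sessions, the regression would extrapolate to every lower count.

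**Conclusion.** The point holds in conditional form. If withdrawn students are not post-tested, the listed model gives them values learned from students with at least 22 of 24 sessions, and neither named check can reveal the error. For a single arm, as an illustration only, 15% withdrawn with half the gain kept overstates the mean gain by 0.15 × 0.5 = 7.5%, or 15% if none is kept. That is not a between-arm bias.

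Between arms the bias may be nil, upward or downward. With the listed predictors it ran from −0.22 to +0.20 SD against an assumed fully trained difference of 0.674 SD. Withdrawal by arm, retained gain, overall gain and the spacing of means are all assumptions. The documents do not support a claim that the trial will favour one arm. They support the narrower conclusion that the primary result would depend on an unstated follow-up practice and on whether group enters the imputation model. This should be corrected before analysis, though it does not undermine the design.

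**What to change.** 1. State that students withdrawn from training remain in follow-up and are invited to the planned post-intervention assessment, subject to consent and the protocol's own safety provisions. If they are already meant to be tested, one sentence saying so resolves most of the point.
2. Use multiple imputation for the ITT analysis without first requiring a judgement that data are missing at random. Put treatment group in the imputation model. Add attendance as an auxiliary variable only if outcomes are obtained from withdrawn students.
3. Add one sensitivity analysis that shifts the imputed values by a delta, separately by arm, over a range stated in advance.
4. Reconcile the attendance limit in Table 1 with the 80% limit in the adherence section. At present a student with three or four missed sessions meets the attendance part of the adherence definition and is also to be withdrawn.

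Cost: some effort to test withdrawn students, who are on the same campus, one extra analysis run, and changes of wording. Treatment group and attendance are already recorded.

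### The listed imputation predictors leave out allocated group; if the list is the whole model, the primary ITT contrasts shrink towards no difference

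*Protocol article*

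**What the plan says.** All of the relevant text is in the Statistical analysis section of the protocol article, apart from the dropout figure.

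- Primary analysis: "The primary analysis will be based on the intention-to-treat principle, and the per-protocol analysis will be used as a sensitivity analysis". The intention-to-treat set is everyone randomized, in the allocated group.
- Missing data: "Missing data will be handled using multiple imputation when the missingness mechanism is considered missing at random".
- Imputation model: "Baseline knee muscle strength, dynamic balance index values, age, height, and weight will be considered predictor variables for imputation". Then: "Five imputed datasets will be generated using a multiple linear regression model in SPSS 25.0". Then: "Pooled estimates will be calculated according to Rubin’s rules".
- Comparison that uses the imputed data: "Between-group differences will be assessed using one-way ANOVA for parametric data", with adjusted pairwise comparisons after a significant overall test.
- Fallback: "If missing data are minimal, complete-case analysis may be reported as a supplementary analysis".

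Allocated group does not appear among the predictors, and no section says that arms are imputed separately. The Sample size section anticipates dropout of about 15%.

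**The concern.** An imputation model should contain the variable whose effect the analysis estimates. Here that variable is the arm. The listed predictors are mainly baseline measurements and body characteristics, which randomization balances in expectation, so they say nothing about which training a participant received. A participant in the combined arm with no post-test would be given a value typical of all three arms together. Every imputed dataset carries the same distortion, so pooling over datasets does not remove it.

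The distortion falls on the primary result, because complete-case analysis is only an optional supplement. It also bears on the plan's own condition for imputing: if both dropout and outcome differ by arm, the data are in general not missing at random given only the listed predictors.

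The direction matters for interpretation. The hypothesis is that the combined programme is superior, and the Discussion says that a result of no added benefit would be informative as well. A method that pulls contrasts towards zero makes that second conclusion easier to reach wrongly.

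**Working it through.** **Inputs from the protocol article.** Three arms, 1:1:1 (Randomization and allocation concealment). Cohen's f = 0.55, alpha 0.05, power 0.90, 16 per group, 15% dropout, 19 per group enrolled, 57 in total (Sample size). Five imputations by linear regression and a threshold of 0.05/3 for each primary outcome (Statistical analysis).

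**Assumptions not in the article.** Baseline-to-post correlation 0, 0.5 or 0.8. Outcomes missing completely at random within arm. Missing fractions of 5%, 15% and 30%. The simulated imputation model held one baseline value and three covariates unrelated to outcome.

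**1. The plan's own figure.** One-way ANOVA power from the noncentral F distribution, k = 3, noncentrality N x f^2: 15 per group gives 0.9001 and 16 gives 0.920. So 16 per group is adequate. Then 16/0.85 = 18.8, rounded up to 19, and 3 x 19 = 57. The figure is reproduced.

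**2. Size of the contrast implied by f = 0.55.** If only the combined arm differs, the difference is 0.55 x 3/sqrt(2) = 1.167 SD. If the arm means are equally spaced, the extreme difference is 0.55 x 2 x sqrt(1.5) = 1.347 SD.

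**3. Expected contrast without arm in the model.** Let d be the missing fraction in every arm, m_g the true mean of arm g and m the mean over arms. After imputation, arm g has expected mean (1 - d) x m_g + d x m. The term d x m cancels in any difference, which leaves (1 - d) x (true difference). At d = 0.15 a true 1.167 SD becomes 0.85 x 1.167 = 0.99 SD.

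**4. Unequal missingness.** Now m is weighted by the observed fractions. Take true means (0, 0, D) in the order TCC, URT, T + URT.

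- Missing 5/5/30%: m = 0.70D/(0.95 + 0.95 + 0.70) = 0.269D. Contrast = 0.70D + 0.30 x 0.269D - 0.05 x 0.269D = 0.77D. Simulated: 0.75.
- Missing 25/15/5%: m = 0.95D/(0.75 + 0.85 + 0.95) = 0.373D. Contrast = 0.95D + 0.05 x 0.373D - 0.25 x 0.373D = 0.88D. Simulated: 0.87.

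**5. Simulation with equal missingness.** 19 per arm, 1,500 trials per setting, five imputations, all three correlations and both patterns of means. Share of the true T + URT minus TCC difference that is kept:

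| Missing | Arm omitted | Arm included |
|---|---|---|
| 5% | 0.93-0.96 | 0.99-1.02 |
| 15% | 0.83-0.85 | 0.99-1.02 |
| 30% | 0.69-0.71 | 0.99-1.02 |

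The last column gives one range for all settings. The correlation hardly matters. With 400 per arm the shares without arm are 0.85 at 15% and 0.70 at 30%, so this is not a small-sample effect. A separate set of runs with correlation 0.6 gave 0.885, 0.842 and 0.698 at 10%, 15% and 30% missing.

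**6. Overall test at 15% missing, 19 per arm.** The test was pooled with the multivariate Wald form of Rubin's rules.

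| | Arm omitted | Arm included |
|---|---|---|
| Power at 0.05 | 0.78-0.81 | 0.91-0.94 |
| Power at 0.05/3 | 0.59-0.63 | 0.82-0.87 |

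The loss is about 13 points at 0.05 and about 23 points at 0.05/3. With no true difference, the test without arm rejected in 0.022-0.031 of trials at nominal 0.05, so it is conservative.

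**The case against.** The strongest reply is that the list need not be closed. The sentence names variables to be considered and does not say that there are no others. The text is a journal article, and a full specification of the imputation model may stand in an analysis plan that is not shown. This stands in part: a reader might infer that the primary analysis will certainly be biased, and the article does not establish that. The conclusion has to be conditional on the list being the model. But this is more than detail left out. The article gives a list that goes down to height and weight, and an analyst who follows it would leave arm out.

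Second, the balance indices on the list might include post-intervention values, which could carry some information about arm. That is possible, but strength and balance share one post-intervention testing window, so a participant who misses one would usually miss both.

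Third, 15% is an anticipated dropout rate used to enlarge the sample. It is not a stated rate of missing outcomes. A participant who stops training could still attend the post-test. This stands, so the 15% figures are an upper case for that dropout rate, and at 5% missing the loss is small.

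Fourth, the bias is conservative. This also stands. A reader might infer that the omission could produce a false claim of superiority, and the calculations show the opposite.

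Three further inferences are not supported. Five imputations are not shown to cause an error: with arm included, five kept practically the whole effect. Nor are Rubin's rules shown to be misapplied: the plan pools estimates, which is their proper use, and an overall test can be pooled too. And nothing in this point calls for replacing the planned ANOVA by a covariate-adjusted analysis.

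**Conclusion.** The point holds in conditional form. If the published predictors are the imputation model, missing outcomes are drawn from an all-arm regression and the primary contrasts are biased towards no difference. Retention is (1 - missing fraction) only when missingness is equal across arms; otherwise it depends on the pattern. For the 1.167 SD difference, 15% missing in every arm costs about 0.15 x 1.167 = 0.18 SD, and power at the plan's per-outcome threshold falls to about 0.6.

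These sizes rest on outcomes missing completely at random within arm and on an assumed range of correlations, to which they are insensitive. If few post-tests are missed, the effect is small. It is still worth correcting before any analysis, because it concerns the primary estimate and the correction is simple.

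**What to change.** State that allocated group is a predictor in the imputation model, or that imputation is done separately by arm, and that the planned between-group contrasts with their standard errors are pooled by Rubin's rules.

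Of the two routes, adding arm as a categorical predictor is the easier. The listed predictors could amount to 12 variables: three strength measures, six balance values (three indices, eyes open and eyes closed), age, height and weight. At 15% missing there would be about 19 x 0.85 = 16 observed outcomes per arm, so regression within arm would need a shorter list.

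Blinding is not affected. The analysts can use the coded arm, which they need in any case for the ANOVA. The cost is one sentence of text and negligible computing time.
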